## Incentives

Incentives will be provided in this study to compensate participants for their time, inconvenience, and discomfort, which is standard research practice for studies of this nature, and we believe is necessary to maintain participation. All participants will be offered an incentive of free basic blood tests including glucose control and cholesterol at enrolment (if no contemporaneous results), 6-months and 9-months. Laboratory test results will be given back to each participant. If a result falls out of its reference range, our research team will advise the participant to seek medical consultation for further assessment. All participants will also be provided with a pedometer to track their physical activity. In addition, they will be offered an incentive of a gift voucher valued at HKD 50 gift coupon upon: (1) completion of study enrolment and (2) completion of the study. Participants in the two intervention groups will receive up to HKD 1,000 cash as the intervention being administered.

# Selection and Withdrawal of Subjects

## Subject inclusion criteria

- Chinese adults aged 30-70 years.
- Capable of providing informed consent.
- Resident in Hong Kong.
- Able to communicate in English or Chinese.
- Diagnosed with type 2 diabetes within past year.
- 6.5% ≤ HbA1c ≤ 9%.
- Willing to take blood tests.
- Access to a smartphone to track physical activity and receive text messages.
- Physically mobile for duration of the trial.

The inclusion criteria of HbA1c ≤ 9% is in accordance with the Hong Kong reference framework for diabetes care recommendation of insulin for HbA1c > 9%^5^.

## Subject exclusion criteria

- Planned surgery in the next 6 months.
- Biological impairment or health condition affecting the ability to walk, such as blindness, physical immobility, and paralysis.
- Pregnant or breastfeeding.
- On insulin for diabetes control.

## Subject withdrawal criteria

Participants are free to withdraw their consent and participation at any stage of the study with no explanation and without any prejudice. If the participant chooses to withdraw, the reasons for withdrawal and participant health status will be recorded. Participants who pass away during the study period will be identified and recorded through interview with the participant’s family member or friend, or identified from hospital records or death certificates, and abstracted from death certificates from Deaths Registry at the end of the study.

# Interventions to be Administered

All participants will receive standard care including patient screening and education on diet, physical activity, and smoking conducted by a multi-disciplinary team ^18^. Arm A (financial intervention) will receive (loss-framed) financial incentives, in addition to weekly feedback on performance for 6 months; Arm B (financial and social interventions) will receive (loss-framed) financial incentives and social incentives, in addition to weekly feedback on performance for 6 months; Arm C (control) will receive no additional intervention during the trial.

The financial incentives use a loss-framed design based on the motivation of loss aversion and the endowment effect. Loss-framed incentives are more effective at increasing physical activity compared to lottery-framed incentives or gain-framed incentives ^22^. Participants randomized to the intervention arms are credited with HKD 1,000 in their viewable virtual account at the beginning of the intervention for the endowment effect during the first two weeks. After baseline step counts are gathered in the second week, participants will lose HKD 40 for each subsequent week of non-adherence to physical activity. Non-adherence is defined as not meeting their personal weekly step target. The amount of financial incentives is small compared to the expected direct medical cost of diabetes to the public sector in Hong Kong of HKD 11,919 (USD 1,521) per year for a person without any complications ^23^.

The social incentives are peer comparison and social support. Since the participants have personalised target step counts, we will not compare direct step counts but rather assess whether they met or exceeded their target. We will feedback the percentage of participants who met or exceeded their targets. We expect the periodic reminders will lead participants to conform their behaviour closer to the social norm. For social support, we will share the participants’ weekly performance with their nominated supporter to act as a social incentive. The nominated supporter is anticipated to encourage the participants to meet their target.

Feedback messages will be positively framed and sent weekly to garner encouragement. Participants enrolled in intervention arm A (financial incentives) with their daily step count target met will receive individualized feedback by text message: “Well done and congratulations! You achieved your physical activity goal this week! You have $1,000 remaining in your account.”. The remaining participants in this arm will be told the balance in their account after penalty of losing HKD40: “Sorry, you did not meet your physical activity goal this week. You lost $40 from your account. Remaining balance = $960.”. Participants achieving their daily step-count target in intervention arm B (financial and social incentives) will receive weekly monitoring and individualized feedback during the incentive period by text message: “Well done and congratulations! You achieved your physical activity goal this week! X% of all participants met their targets this week (X% exceeded!). You have $1,000 remaining in your account.”. Those not meeting their targets in this arm will be told they did not meet their targets and the balance in their account after penalty of losing HKD40: “Sorry, you did not meet your physical activity goal this week. X% of all participants met their targets this week (X% exceeded!). You lost $40 from your account. Remaining balance = $960. Keep it up and strive for your best next week!”.

Participants who are not able to record and share their step counts on a weekly basis will receive messages or phone calls from the research team to record their physical activity performance. The incentives are discontinued during the post-intervention follow-up period.

Participants being enrolled in the control arm will not be told their baseline step count after the second week. They will receive the routine care but not weekly feedback nor messages.

## Medications permitted and not permitted before and/or during the study

Participants eligible for the study must be newly diagnosed with diabetes within a year. Participants can continue taking other medication, treatment or routine for conditions other than diabetes should they be enrolled at any time of the study. Participants are allowed to initiate additional medication for glycaemic control during the 6-month follow-up period, and other medication including agents to control lipid levels or blood pressure. The inclusion criteria of HbA1c ≤ 9% is in accordance with the Hong Kong reference framework for diabetes care recommendation of insulin for HbA1c > 9%^5^.

## Stopping rule

Given that the study interventions are non-invasive and non-clinical, we do not plan to conduct any interim analyses to inform whether to continue the study. However, if we observe any SAEs confirmed by a physician where appropriate, we will terminate participation for the participant and conduct an immediate investigation while suspending the trial until a satisfactory resolution.

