## Follow-up assessments

A follow-up assessment on health information, similar to the baseline enrolment questionnaire, including body weight and height, general health, medication usage and health service usage will be collected when participants have blood drawn 6 months after enrolment. In usual practice, newly diagnosed patients with type 2 diabetes attend regular medical appointment every 3 months to monitor their condition. A brief follow-up assessment will be completed at 9 months for all participants to monitor changes in health status of the participants longitudinally.

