# Outcome Measures

## Primary outcome

Glycaemic control defined as the change in HbA1c levels at 6-months (and 9-months) compared to baseline levels. HbA1c levels reflect the average glucose level over the past 2-3 months (not influenced by daily fluctuations) and has strong predictive value for diabetes complications^5^.

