## Secondary outcomes

The secondary outcome measures at 6-months and 9-months include:

- proportion of participants with good/excellent diabetes control (HbA1c threshold ≤7% & ≤6.5%)
- change in body weight and body mass index
- changes in lipid profile (HDL- and LDL-cholesterol) and blood pressure
- proportion of participants requiring initiation of additional medication or higher dose adjustment for glycaemic control
- proportion of smokers quitting
- change in level of physical activity (step count)
- change in health care attendances and admissions

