# Assessment of Safety

Participants should report any adverse events to the study co-ordinator (contact details are provided to participants). Given the non-clinical nature of the intervention, we do not anticipate any occurrence of SAEs within our study. We will survey participants for any safety issues at 6-months and 9-months after enrolment. We will record and inform the IRB of any reported adverse events. For stopping rule, refer to section 6.2 for details. All trial-related activities including enrolment and follow-up will be conducted by our delegated research team members from the School of Public Health, the University of Hong Kong.

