## Selection of participants to be included in the analyses

We will follow an intention-to-treat approach in the analyses; therefore all randomized participants will be included.

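### The stopping rule ends participation after any SAE without saying that 6- and 9-month outcomes are still collected, which invites avoidable, health-related missing HbA1c data

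*Protocol*

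**What the plan says.** - **Stopping rule** (under Interventions to be Administered): on any SAE, with a physician's confirmation where appropriate, "we will terminate participation for the participant and conduct an immediate investigation while suspending the trial". The rule is not limited to events related to the intervention.
- **Selection of participants to be included in the analyses:** "We will follow an intention-to-treat approach in the analyses; therefore all randomized participants will be included".
- **Primary outcome:** "Glycaemic control defined as the change in HbA1c levels at 6-months (and 9-months) compared to baseline levels". This needs a later blood draw.
- **Secondary outcomes**, at 6 and 9 months, include "change in health care attendances and admissions".
- **Follow-up assessments:** "medication usage and health service usage will be collected when participants have blood drawn 6 months after enrolment". A brief assessment follows at 9 months.
- **Subject withdrawal criteria:** reasons and health status are recorded when the participant chooses to withdraw. Participants terminated by the study team are not mentioned.
- **Procedure for accounting for any missing data:** multiple imputation with 10 datasets (20 if needed). The named predictors are HbA1c at the three time points, weight, age and sex.
- **Figure 1:** 87 per arm allocated, 13 discontinued or lost, 74 analysed.
- **Assessment of Safety:** "we do not anticipate any occurrence of SAEs within our study". The protocol gives no SAE rate and does not define the term.

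**The concern.** Stopping an intervention and stopping measurement are separate decisions, and the stopping rule does not separate them. An intention-to-treat comparison is best supported when everyone randomised is measured, whatever happened after randomisation. If an SAE ends study participation altogether, the trial creates missing HbA1c values itself, and does so in people selected by a serious health event. HbA1c may well be related to that event, so the missingness would be informative. Imputation would then stand in for measurements that visits already in the schedule could have provided.

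Health-service use has the same weakness. It is collected at the 6-month blood draw, so a participant terminated before then has no stated collection point. If admissions are treated as SAEs, a person would be removed at the first occurrence of the event being counted.

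**Working it through.** **1. What does participation mean in the stopping rule?** Three points favour study participation over the incentive alone.
- Subject withdrawal criteria and Ethics both use the word for being in the study.
- Arm C receives no added intervention (Interventions to be Administered), so for a control participant there is nothing else to terminate.
- Where the protocol means only the incentives, it says that the incentives are discontinued.

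No section keeps a terminated participant in outcome follow-up.

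**2. How would such a participant be analysed?** The text includes everyone randomised, with missing outcomes imputed. Figure 1 shows 87 − 13 = 74 analysed per arm, so discontinued participants are subtracted. The two do not agree, and a participant terminated after an SAE would most naturally fall among the 13. (Separately, 13/87 = 14.9% does not match the 10% in the text.)

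**3. The plan's own sample size.** Inputs from Sample size justification: difference 0.6, SD 1.5, alpha 0.05, power 80%, dropout 10%.
- n per group = 2 × (z_alpha + z_0.80)² × (1.5/0.6)².
- One-sided 0.05: 2 × (1.645 + 0.842)² × 6.25 = 77.3, so 78. This matches the plan.
- Two-sided 0.05: 2 × (1.960 + 0.842)² × 6.25 = 98.1, so 99. This does not match, and is a separate matter.
- 78/0.90 = 86.7, so 87 per group; 3 × 87 = 261. This matches.

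**4. How many participants?** The rate r is an assumption: 5 to 10% per year. Participants with at least one SAE by time t number 261 × (1 − exp(−r × t)).

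| t | r = 5% | r = 10% |
|---|---|---|
| 0.5 years (before month 6) | 6.4 (2.5%) | 12.7 (4.9%) |
| 0.75 years (before month 9) | 9.6 | 18.9 |

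Against a 10% allowance of 26.1 people, the month-6 figures are 6.4/26.1 = 25% and 12.7/26.1 = 49%.

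**5. Power if these losses come on top of the 10%.** Two-sided t-test at 0.05, effect size 0.6/1.5 = 0.4.

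| Extra loss | Evaluable per arm | Power |
|---|---|---|
| 0% | 78.3 | 0.701 |
| 1% | 77.4 | 0.696 |
| 2% | 76.6 | 0.691 |
| 5% | 74.0 | 0.676 |

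Each 1% removes about 0.9 people per arm (2.6 in all) and costs about half a power point.

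**6. Admissions, only if they count as SAEs.** As an illustration, take true proportions of 10% and 5%, with half of those admitted removed without further data. Completers then show 0.050/0.950 = 5.3% and 0.025/0.975 = 2.6%. The difference appears as −2.7 points instead of −5.0. If every admission led to removal, completers would show none in any arm.

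**The case against.** **The rule contradicts intention-to-treat.** A reader might infer this, but the documents do not support it. The intention-to-treat statement fixes who is analysed, and imputation is a stated way of keeping unmeasured participants in. The protocol also expects some non-completion. What stands is a tension.

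**The sickest participants lose all their outcome data.** This too goes beyond the text. The rule sits under interventions and does not mention blood draws or data, so a narrower reading is possible, although the wording favours the wider one. An SAE after month 6 leaves the 6-month HbA1c already collected. Safety is surveyed at 6 and 9 months, so an SAE first learned of at the 6-month visit need not cost that sample. The 10 to 19 participants expected over nine months at the assumed rate therefore should not be quoted for the 6-month endpoint.

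**Admissions and the expectation of no SAEs.** The conflict with the admissions outcome needs an SAE definition that the protocol does not give. The expectation of no SAEs is tied to the non-clinical nature of the intervention, so it can be read as concerning events the intervention causes. It is not shown to conflict with counting admissions.

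**Size.** The rate is assumed, the losses could fall within the existing 10% allowance, and no difference in SAEs between arms is shown. Arms A and B have weekly contact that controls lack, so SAEs might surface sooner there; that is inference only. Material bias in the HbA1c comparison is possible but not demonstrated.

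**Imputation.** The predictor list says what the model will include, so others could be added. As stated, though, it has no SAE, admission or reason for discontinuation, and a richer model would still replace data that could be collected.

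**Conclusion.** The point holds as a defect in what the protocol fixes: one SAE of any cause triggers termination, and nothing provides for outcome data afterwards. This conclusion needs no SAE rate. It rests on reading participation as study participation, which the protocol's own usage supports. The result is avoidable missing HbA1c data related to health, which the named imputation predictors do not capture, and Figure 1 adds doubt about whether these people are analysed at all.

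The number affected is unknown. At the assumed 5 to 10% per year it is about 6 to 13 of 261 before month 6. Even 5% lost on top of planned dropout lowers two-sided power only from 0.701 to 0.676, so the weight of the point is in selection. Truncation of the admissions outcome is conditional on admissions counting as SAEs.

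**What to change.** Reconcile Figure 1, Follow-up assessments, Subject withdrawal criteria, Stopping rule, Secondary outcomes, the missing-data procedure and the analysis-population statement. Separate data collection from the clinical stopping decision:
- After an SAE, HbA1c and health-service data are still collected at the planned 6- and 9-month visits unless consent is withdrawn.
- The participant is analysed in the randomised arm, and Figure 1 is brought into line with the statement that everyone randomised is included.

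Whether an SAE stops the incentive or suspends the trial is left to the investigators and the Data Monitoring Committee; no clinical rule is proposed here. The cost is protocol wording. The visits are already scheduled, and if terminated participants stay in follow-up the target of 261 needs no change on this account.

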Arm A (financial incentives): Participants will receive the usual standard care (same as control group), a loss-framed financial incentive, and weekly feedback on performance for 6 months.

Arm B (financial and social incentives): Participants will receive the usual standard care (same as control group), a loss-framed financial incentive, social incentives, and weekly feedback on performance for 6 months.

Arm C (control): Participants will receive standard care under the risk factor assessment and management programme (RAMP) including patient screening and education on diet, physical activity, and smoking conducted by a multi-disciplinary team ^18^.

The study will last for a total of 36 months including a 11-month suspension due to COVID-19 pandemic. This includes a 11-month recruitment period on rolling basis, 9-month follow-up period for each participant (consisting of 6-months intervention period and 3-month post-intervention period) and 3-month buffer for any rescheduling of follow-up. We plan to allow 4-months for the data analysis and 3-months to write-up our findings.

The pragmatic study design is based on the PRECIS-2 tool (Appendix 3) and RE-AIM frameworks.^19,20^ This trial is registered at ClinicalTrials.gov and will follow this pre-specified protocol.

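### As worded, the stopping rule suspends the whole trial for any serious adverse event, related to the intervention or not

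*Protocol*

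**What the plan says.** The trigger in Stopping rule (section 6.2) is: "if we observe any SAEs confirmed by a physician where appropriate". Two consequences follow. The affected person's participation ends, and the team will "conduct an immediate investigation while suspending the trial until a satisfactory resolution". Because the participant's own exit is stated separately, the second consequence is most naturally read as a pause of the whole trial.

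Assessment of Safety states that "we do not anticipate any occurrence of SAEs within our study", giving the non-clinical nature of the intervention as the reason, and refers back to section 6.2. Detection rests on two routes: "Participants should report any adverse events to the study co-ordinator", and "We will survey participants for any safety issues at 6-months and 9-months after enrolment". All reported adverse events go to the IRB.

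The Ethics section plans an independent Data Monitoring Committee that reviews safety and outcome data periodically. It gives the committee no part in suspending or resuming the trial.

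**The concern.** The physician confirms that an SAE occurred, and only where appropriate. Nobody is asked whether the incentives, the step targets or a trial procedure caused it. SAE is not defined in the text shown. Under the usual all-cause meaning, an unrelated hospital admission would halt the trial. The protocol itself expects admissions, since one secondary outcome is "change in health care attendances and admissions".

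A halt does not fall evenly on the arms. Only arms A and B receive weekly feedback and deductions; arm C receives usual care without messages. If participants' 6-month clocks run on during a halt, arms A and B lose treatment weeks and the contrast with arm C shrinks. If the clocks stop, HbA1c visits move, which the "3-month buffer for any rescheduling of follow-up" in Study Design partly absorbs. When the event is unrelated, neither cost buys any safety.

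The same sentence also removes the affected participant for any SAE. That sits badly with the commitment, under Selection of participants to be included in the analyses, to analyse everyone randomised by intention to treat. A participant removed before 6 months has no HbA1c value and must be imputed.

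**Working it through.** **Does any section narrow the trigger?** No stated figure is at issue, so the first check is of the text.

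| Protocol section | What it contributes | Relatedness condition? |
|---|---|---|
| Stopping rule (6.2) | Any SAE, physician-confirmed where appropriate, leads to suspension | No |
| Assessment of Safety | No SAEs expected; refers back to 6.2 | No, though its reasoning hints at related events |
| Subject withdrawal criteria | Deaths are identified and recorded | No; not linked to the rule |
| Quality Control and Quality Assurance | Strict compliance with the protocol | No; it binds staff to the wording |
| Ethics | Data Monitoring Committee reviews safety | No; no role in suspension |

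**How likely is an SAE to occur?** The protocol gives no SAE rate, so the rates below are assumptions, shown as a range.

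Inputs: 261 randomised (Randomization) and 9 months of follow-up, 6 of them intervention (Study Design).

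- Exposure, all follow-up: 261 × 0.75 = 195.75 person-years.
- Exposure, intervention period: 261 × 0.5 = 130.5 person-years.
- P(at least one) = 1 − exp(−rate × person-years).

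| Assumed rate of unrelated SAEs per 100 person-years | Expected, 9 months | P, 9 months | P, intervention period only |
|---|---|---|---|
| 0.5 | 0.98 | 62% | 48% |
| 1 | 1.96 | 86% | 73% |
| 2 | 3.92 | 98% | 93% |
| 5 | 9.79 | >99.9% | 99.9% |

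The chance passes one half at ln(2)/195.75 = 0.35 per 100 person-years over all follow-up, and at ln(2)/130.5 = 0.53 in the intervention period. These exposures are maxima. If the 10% assumed lost contributed no time at all, exposure would be 0.9 × 195.75 = 176.2 person-years, and at 1 per 100 the chance would be 1 − exp(−1.762) = 83%.

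**From occurrence to an observed event.** The rule acts only on events that the team observes. An unreported event may surface only at the 6- or 9-month survey, and a death first found in the registry at the end of the study would halt nothing. Let d be the assumed share seen in time. For the intervention period at 1 per 100 person-years, P = 1 − exp(−0.01 × 130.5 × d): 73% for d = 1, 48% for d = 0.5 and 28% for d = 0.25. The protocol gives no basis for choosing d.

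**What a halt would cost.** As an illustration only: six months is about 26 weeks, and the first two set the baseline, which leaves 24 deduction weeks. If clocks ran on, each suspended week would remove 1/24 = 4.2% of those weeks for a participant then in that period. Turning this into a change in the HbA1c difference would need the number and length of halts, the enrolment pattern over the "11-month recruitment period on rolling basis", the clock rule, and how the effect depends on weeks delivered. The protocol supplies only the planned recruitment length, so no effect on the planned −0.6 is calculated.

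**The case against.** The strongest reply is that pausing first and investigating second is a defensible, conservative choice. The intervention pushes adults up to age 70 with diabetes towards 10,000 steps a day, and a fall or cardiac event cannot be called unrelated until someone has looked. This stands for events whose cause is unclear, so the threshold in the fix is at least possible relatedness. It does not justify a trial-wide pause for an event that is plainly unrelated.

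A second reply is that the authors meant study-related events. Inferring from a non-clinical intervention that no SAEs will occur makes sense only on that reading. This may well be right, and it lowers the stakes. But the rule does not say it, and with strict compliance required, staff facing an unrelated admission must either halt the trial or deviate from the protocol.

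Third, the harm is speculative, and this largely stands. A reader might take 86% as the chance that the trial is halted. It is the chance that an event occurs at one assumed rate; the chance of an observed halt is lower and cannot be derived. A reader might also infer a definite dilution of the primary effect. That requires clocks to run on, which the protocol does not say; the one suspension it describes, for COVID-19, was added to the study calendar. Nothing here points to a false positive.

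Finally, the last logged change is dated September 2022 and the study period ends in December 2022, so a late amendment may protect few incentive weeks. That limits the benefit without making the wording right.

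**Conclusion.** The point holds as a badly fixed rule: the written trigger is wider than safety requires, and the sections shown do not narrow it. That conclusion rests on the text and needs no rate. That the trigger would probably be met at least once rests on an assumed rate of unrelated SAEs, the usual all-cause definition and near-complete follow-up.

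The consequence is low. A short pause would do little harm; repeated or long pauses would cost more, but the protocol gives no way to predict their number or length. The document does not support a claim that the trial is bound to stop, or that the HbA1c comparison will be biased by a stated amount. This is a cheap improvement and no threat to the trial's validity.

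**What to change.** Amend Stopping rule (section 6.2) as follows:

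- Every SAE gets prompt individual review, including a judgement of causality.
- The trial is suspended only for an SAE judged at least possibly related to the intervention or trial procedures, or on the recommendation of the Data Monitoring Committee. The committee also decides on resumption.
- For the affected participant, the intervention is stopped where clinically indicated, in place of automatic removal. The 6- and 9-month HbA1c assessments are kept for all randomised participants, provided that consent continues and the assessment procedure did not cause the event.

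The cost is one amendment with IRB agreement, using a committee already planned. The downside is that a causality judgement must come before any trial-wide pause, which can mean a short wait.
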